**Fig. 1 Fig1:**
[figure not shown]
CONSORT diagram

### Data collection

Table 2 displays the schematic diagram for the timeline of patient assessment and data collection. Assessment on localization accuracy and safety will be performed by research physicians and recorded by the research nurse within 30-days after the laparoscopic colectomy. All information should be recorded in Case Report Form (CRF) in a timely, truthful and detailed manner. Researchers must input information into the CRF according to protocol requirements, and supervisors appointed by the research center will check the completeness and accuracy of the CRF and guide the research center personnel to make necessary modifications or additions. CRF will hand over data entry to a reliable medical data processor. Text items can only be checked manually after they are entered into the database from CRF. The data manager performs system checks on the information entered the database. Data will be locked upon completion of entry. Any subsequent changes to the database may only be made with the joint written consent of the clinical study leader, the study statistician, and the data manager.

**Table 2 Tab2:** Schematic diagram for the schedule of enrolment, interventions, and assessments

TIMEPOINT	STUDY PERIOD			
	Enrolment	Allocation	Post-allocation	
	−1 to −2 weeks	0	1 week	2 weeks
ENROLMENT:				
Eligibility screen	X			
Informed consent	X			
Allocation		X		
INTERVENTIONS:				
*Autologous blood*			X	
*Intraoperative colonoscopy*			X	
ASSESSMENTS:				
*Physical examination*	X		X	
*Laboratory tests*	X		X	
*Oncology assessment*	X			
*localization accuracy*			X	
*Surgical safety*				X

### Sample size and statistical analysis

The primary objective of this study is to identify non-inferiority of autologous blood tattooing versus intraoperative colonoscopy group. Based on our current experience and previous studies which reported the rates of successful visualization, success rates of 99 and 95% were assumed for the intraoperative colonoscopy group and the autologous blood group, respectively. With settings of 80% power, 5% significance level, and non-inferiority margin of 10%, sample sizes of 110 patients in each group will be required.

Continuous variable will be presented as mean and SD if normally distributed, or as median and range otherwise. The differences between the groups were assessed using the t-test, the Mann-Whitney test, Fisher’s exact test, or the χ2 test, as appropriate. Multivariate analysis to assess the impact of potential con- founding factors (sex, age, body mass index, endoscopist, tumor location [colon vs. rectum], clinical tumor stage [≥ T2 vs. T1 or scars]) on invisible tattoo will be performed by using a logistic regression model. All tests will be two-sided with a significance level of *P* < 0.05. All statistical analyses will be carried out using SPSS software package (version 22.0; SPSS Inc.).

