After completing an initial assessment and signing an informed consent form, participants will be randomized with 1:1 ratio into two groups: autologous blood marker group and intraoperative colonoscopy group. The data manager, who will not be involved in eligibility assessment and recruitment of patients, will perform the randomization with a list of randomly ordered treatment identifiers generated by a permuted block design using SAS (version 9.1; SAS Institute Inc.). Although it will not be feasible to blind the surgeons and participants, the researcher performing the statistical analyses will be blinded to the patient group allocation.

This protocol and the informed consent forms have been reviewed and approved by Shanghai East Hospital and Institute Ethics Review Committee. We will obtain a new approval from the Committee if any amendments are made to the protocol or the informed consent form that may have an impact on the conduct of the study or potential benefit of the patient. A signed consent must be obtained from every participant in the ancillary study, if the data collection/request is not covered in the original informed consent process for the main clinical trial. The study has been registered in Clinical-Trial.gov (NCT05597384).

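### At the plan's two-sided 5% level, 110 per group gives about 75% power, not 80%; the number suffices only for a one-sided 5% test that the plan does not describe

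*Protocol article*

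**What the plan says.** All of the relevant text is in the protocol article, mainly under Sample size and statistical analysis.

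- Assumed rates: "success rates of 99 and 95% were assumed for the intraoperative colonoscopy group and the autologous blood group, respectively".
- Sample size: "With settings of 80% power, 5% significance level, and non-inferiority margin of 10%, sample sizes of 110 patients in each group will be required". This sentence does not say whether the 5% is one-sided or two-sided, and it mentions no allowance for losses.
- Level of the analysis, in the next paragraph: "All tests will be two-sided with a significance level of" 0.05. The non-inferiority comparison is not excepted, and no one-sided test appears anywhere in the article.
- Allocation, under Study design and setting, and participant: "participants will be randomized with 1:1 ratio into two groups". The Abstract gives the total as 220.

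**The concern.** A non-inferiority test looks at one side of an interval only. A two-sided 5% level therefore means one-sided 2.5%, and a one-sided 5% level means a 90% interval. The two need different sample sizes, and the article's 110 does not match the level that the article itself sets.

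Two things are at stake. First, the 220 patients are justified by a power that the planned test does not have, so an inconclusive result is more likely than the plan admits and could be taken as evidence against autologous blood. Second, if the level can be read either way, the same data could pass with a 90% interval and fail with a 95% interval, and the plan does not settle in advance which one counts.

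**Working it through.** **Inputs** (all from the sample-size paragraph): control rate 0.99, autologous blood rate 0.95, margin 0.10, power 80%, 1:1 allocation. The expected difference is 0.04, so the distance to the margin is 0.10 − 0.04 = 0.06. The variance term is 0.99 × 0.01 + 0.95 × 0.05 = 0.0099 + 0.0475 = 0.0574.

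**Formula** (unpooled normal approximation): n per group = (z_α + z_β)² × 0.0574 / 0.06².

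**Trying to reproduce 110**

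- One-sided 5%: (1.645 + 0.842)² × 0.0574 / 0.0036 = 98.6, so 99 per group. This is not 110. Dividing by 0.9 for an assumed 10% loss gives 99 / 0.9 = 110. No other route tried gives exactly 110, and the 10% is an inference that the article does not state.
- Two-sided 5% (one-sided 2.5%): (1.960 + 0.842)² × 0.0574 / 0.0036 = 125.1, so 126 per group. This is 16 more per group than planned, before any losses.

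**Other formulas, per group**

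| Method | One-sided 2.5% | One-sided 5% |
|---|---|---|
| Unpooled | 126 | 99 |
| Pooled | 127 | 100 |
| Continuity-corrected | 157 | 130 |
| Farrington-Manning | 190 | 147 |

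Every method at the plan's stated level needs more than 110.

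**Power at 110 per group by the normal approximation**

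The standard error is √(0.0574 / 110) = 0.02284, and 0.06 / 0.02284 = 2.627.

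- One-sided 2.5%: Φ(2.627 − 1.960) = 74.7%.
- One-sided 5%: Φ(2.627 − 1.645) = 83.7%.

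If 110 already contains a 10% loss, 99 per group can be analysed. The standard error is then √(0.0574 / 99) = 0.02408, and power at one-sided 2.5% is Φ(2.492 − 1.960) = 70.3%.

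**Power by exact binomial enumeration**

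The expected failures are 110 × 0.01 = 1.1 in the control group and 110 × 0.05 = 5.5 in the autologous blood group. Counts this small make the normal approximation unreliable, so power was also summed over all possible outcomes.

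| Level and interval | 99 per group | 110 per group | 126 per group |
|---|---|---|---|
| One-sided 2.5%, Wald | 66.6% | 72.8% | 75.7% |
| One-sided 2.5%, Newcombe | 50.4% | 52.1% | 58.0% |
| One-sided 5%, Wald | 74.7% | 78.2% | 85.1% |
| One-sided 5%, Newcombe | 60.5% | 68.1% | 75.8% |

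The Farrington-Manning score test gives the same figures as Newcombe to within 1 percentage point.

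**The case against.** The strongest reply is that the 5% in the sample-size sentence was always meant as one-sided. The sentence on two-sided tests follows a list of difference tests and a logistic model, so it may be standard wording for those analyses only. On that reading 99 is the right base number, and 99 / 0.9 = 110 suggests a correct calculation that was described too briefly. An article may also leave the loss allowance to the full protocol.

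Part of this stands. The one-sided origin is plausible, and the missing loss allowance is not itself a fault. The conflict remains, however: the article says all tests are two-sided, makes no exception and names no one-sided test. One of the two statements has to change.

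A second reply is that the figure of about 52% depends on an interval method that the article does not name and that an analysis plan may settle. That is fair. The error shown by the article's own text is the drop from 80% to about 75%. The score-type figure shows how much further power could fall with one reasonable choice of interval; it is not a second misstatement.

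A third reply is that the type I error is not inflated and that a reported interval would show an inconclusive result for what it is. That is true if the 95% interval is used and reported. It does not make the stated power correct.

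**Conclusion.** The concern holds. Under the article's own rates, margin and two-sided 5% rule, 80% power needs 126 per group by the standard formula, and 110 gives 74.7%. The number is sufficient by that formula only at one-sided 5%, and it is reproduced exactly only with an unstated 10% loss.

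The size of the shortfall depends on two things that the article leaves open:

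- **Interval method.** At 110 evaluable per group and one-sided 2.5%, exact power is 72.8% (Wald) or about 52% (Newcombe or Farrington-Manning).
- **Losses.** If 110 includes an assumed 10% loss, power is about 70% by the formula and about 50% with a score-type interval.

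Even at one-sided 5% with all 110 evaluable, exact power is 78.2% (Wald) or about 68% (score-type), still under 80%. All of these figures take the assumed 99% and 95% as true.

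**What to change.** Choose one of the following and make the sample-size paragraph and the analysis paragraph agree.

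1. **Keep the two-sided 5% rule.** State that non-inferiority is judged by the lower limit of the two-sided 95% confidence interval (one-sided 2.5%), and name the interval method. Restate the power for 110 per group as about 75% by the formula, and about 52% if a score-type interval is used.
2. **Declare one-sided 5% for the primary comparison.** Say so explicitly, report a 90% confidence interval, and exempt the primary analysis from the sentence on two-sided tests. If it is how 110 was derived, state 99 evaluable per group plus 10% loss. Give the exact power for the chosen interval alongside the formula value.

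Both are changes of wording and need no extra patients. The cost is a less favourable power statement under the first option and a more lenient error level under the second.

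If the sponsor wants 80% power at the two-sided level, the formula asks for at least 126 per group, or 126 / 0.9 = 140 with an assumed 10% loss. A score-type interval would need more (190 per group by Farrington-Manning, before losses). That would be a change of design and is not required to correct the statement.

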### Hypothesis

Preoperative endoscopic localization with autologous blood is no inferiority to intraoperative colonoscopy localization in small, serosa-negative lesion which will be performed by laparoscopic colectomy.

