### Assessment of outcomes

#### Primary outcome

The primary outcome is the localization accuracy. While checking the intraperitoneal cavity at the start of the surgery, the visibility of tattooing will be first checked. After the complete resection of the colon segment, resected colon specimen will be checked the localization with autologous blood tattooing. An accurate localization is defined as tumors identified both by visible tattoo during surgery and by pathological examination of the resected specimen.

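### The objective is non-inferiority with a 10-point margin, but the only between-group analyses fixed are two-sided tests of zero difference, and nothing compares the result with the margin

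*Protocol article*

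**What the plan says.** The Hypothesis section of the Protocol article reads "Preoperative endoscopic localization with autologous blood is no inferiority to intraoperative colonoscopy localization". Sample size and statistical analysis repeats the aim: "The primary objective of this study is to identify non-inferiority of autologous blood tattooing versus intraoperative colonoscopy group". The endpoint is binary per patient: "The primary outcome is the localization accuracy", with accurate localization defined as a yes/no result.

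The margin appears once, in the sample-size paragraph: "success rates of 99 and 95% were assumed for the intraoperative colonoscopy group and the autologous blood group", then "With settings of 80% power, 5% significance level, and non-inferiority margin of 10" percent, and "sample sizes of 110 patients in each group will be required". That paragraph does not say whether the 5% is one-sided or two-sided.

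The next paragraph gives the analysis. Group comparisons are described by "The differences between the groups were assessed using the t-test, the Mann-Whitney test", followed by Fisher's exact test and the chi-squared test. A logistic model for factors affecting an invisible tattoo is added. The paragraph closes with "All tests will be two-sided with a significance level of" 0.05. There is no confidence interval for the difference, no margin-based test and no rule for concluding non-inferiority. The interim stopping rule (Data monitoring, auditing, and interim analysis) is also framed as one treatment being better or worse than the other.

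**The concern.** A non-inferiority claim needs the null hypothesis that blood is worse than colonoscopy by at least 10 points to be rejected. Fisher and chi-squared, as listed, test the null that the two rates are equal. A non-significant result does not exclude a loss of 10 points or more. Nor does a significant result show that the loss reaches 10 points.

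The logistic model does not fill the gap. Its outcome is an invisible tattoo, which only the blood group can have, so it does not compare the arms.

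At stake is the trial's main conclusion. The Discussion makes the value of the technique depend on the hypothesis being statistically proved, and the listed tests cannot do that.

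**Working it through.** **Inputs.** From Sample size and statistical analysis: rates of 99% (colonoscopy) and 95% (blood), margin 10 points, power 80%, significance level 5%, 110 per arm. Differences below are blood minus colonoscopy. Chi-squared is uncorrected.

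**1. The plan's own figure.** Unpooled normal approximation:

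n = [pC(1−pC) + pT(1−pT)] (z_α + z_β)² / (margin − (pC − pT))²

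Variance sum: 0.99×0.01 + 0.95×0.05 = 0.0099 + 0.0475 = 0.0574. Denominator: (0.10 − 0.04)² = 0.0036.

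- One-sided 5%: 0.0574 × (1.645 + 0.842)² / 0.0036 = 98.6, so 99 per arm.
- One-sided 2.5%: 0.0574 × (1.960 + 0.842)² / 0.0036 = 125.1, so 126 per arm.

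Neither equals 110. One-sided 5% with 10% dropout does (99 / 0.90 = 110), but no dropout is stated. A superiority calculation at 99% vs 95% needs 285 per arm, so 110 does not come from a superiority design. The intended alpha remains unstated, and both values are carried below.

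**2. Error if non-significance were read as non-inferiority.** Method: sum the products of two binomial probabilities (n = 110 each) over all result tables meeting the criterion, with the true rates exactly on the margin.

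| True rates (colonoscopy vs blood) | Fisher P ≥ 0.05 | Chi-squared P ≥ 0.05 | Newcombe 95% lower limit > −10 | Newcombe 90% lower limit > −10 |
|---|---|---|---|---|
| 99% vs 89% | 11.5% | 6.9% | 1.9% | 4.6% |
| 95% vs 85% | 36.0% | 27.3% | 2.5% | 4.9% |

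The difference tests exceed nominal at both 2.5% and 5%, and their error depends strongly on the control rate. The margin-based limit stays at or below nominal in both rows.

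**3. Single results.**

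- 105/110 (colonoscopy) vs 97/110 (blood): Fisher P = 0.083. The 95% lower limit is −15.1 points (Newcombe) or −14.5 (Wald), so non-inferiority is not shown. Chi-squared gives P = 0.049 on the same table, so the two listed tests fall on opposite sides of 0.05.
- With one more success in the blood arm, 105/110 vs 98/110, both tests are non-significant. Pooled failure rate 17/220 = 0.0773; SE = √(2 × 0.0773 × 0.9227 / 110) = 0.0360; z = 0.0636 / 0.0360 = 1.77; chi-squared P = 0.077 (Fisher 0.13). Wald SE = √(0.9545×0.0455/110 + 0.8909×0.1091/110) = 0.0357. The 95% lower limit is −6.4 − 1.96 × 3.57 = −13.4 points and the 90% limit is −6.4 − 1.645 × 3.57 = −12.2. Non-inferiority is not shown at either level.

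**4. Power of a margin-based rule at 99% vs 95%, 110 evaluable per arm (exact enumeration).**

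| Interval | Power |
|---|---|
| Newcombe 95% | 52% |
| Newcombe 90% | 68% |
| Wald 95% | 73% |
| Wald 90% | 78% |

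The normal approximation gives 74.7% (one-sided 2.5%) and 83.7% (one-sided 5%). Rates this close to 100% make it optimistic.

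**The case against.** The strongest reply is that the tests sentence is a generic list. It follows the descriptive-statistics wording, does not name the primary outcome, and may be meant for baseline and complication comparisons. A condensed article may leave the margin comparison to a full protocol or analysis plan not shown here. Two-sidedness itself is also harmless: a two-sided 95% interval is a standard way to test non-inferiority.

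Part of this stands. A reader might infer that the plan will declare non-inferiority whenever P exceeds 0.05. The document states no such rule, so the error rates above are conditional on that reading. A reader might also take one-sided 2.5% as the intended error rate; the article does not say so.

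Two stronger presentations are also unsupported.

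- Under 99% vs 95%, the share of trials that are non-significant by Fisher yet miss the margin is 24% with the Newcombe 95% limit. It is only 3.5% to 8.8% with Newcombe 90% or Wald limits, so 24% should not stand alone.
- A result such as 110/110 vs 106/110 might be offered as significant yet non-inferior. That holds by chi-squared (P = 0.044) but not by Fisher (P = 0.12), and with an expected 2 failures per arm Fisher is the usual choice.

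The reply does not remove the point. The article does not leave the comparison of groups open: it names the tests and says that all tests follow one two-sided rule. That fixed content does not fit its own objective, and no other section repairs it. An unseen plan might, but the published text would still need to be reconciled with it.

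**Conclusion.** The point holds. As written, the article contains no analysis that can establish its primary hypothesis: the margin enters the sample size and never the analysis. This conclusion needs no assumption about alpha or about how P values would be read.

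The size does need one. If non-significance were taken as non-inferiority, false claims on the margin at 110 per arm would run from 6.9% (chi-squared, 99% vs 89%) to 36.0% (Fisher, 95% vs 85%), above nominal whether 2.5% or 5% one-sided was meant. The 95% vs 85% pair is an illustrative assumption about a lower control rate; the 99% comes from the plan.

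The documents do not support calling 110 per arm wrong, because the sidedness and any dropout allowance behind it are not given.

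**What to change.** Add a primary-analysis statement to Sample size and statistical analysis:

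- Estimate the difference in localization accuracy, blood minus colonoscopy, with a prespecified confidence interval, preferably score-type (Newcombe or Miettinen-Nurminen). Declare non-inferiority only if the lower limit is above −10 percentage points.
- State the interval level so that it matches the sample-size alpha: 95% for one-sided 2.5%, 90% for one-sided 5%. Say which was used to obtain 110, and whether dropout was allowed for.
- Keep Fisher's exact and chi-squared tests for the other comparisons.

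The cost is more than wording. At the planned rates with 110 evaluable per arm, exact power is about 52% (Newcombe 95%), 68% (Newcombe 90%), 73% (Wald 95%) or 78% (Wald 90%), so the stated 80% must be rechecked and restated for the method chosen, and the sample size may have to rise. Choosing Wald to recover power has its own price: at 99% vs 89% the Wald 95% rule has a one-sided error of 4.8% against a nominal 2.5%. Interval method, alpha and sample size should be settled together, before outcome data are seen.

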### Intervention

All patients will receive localization and surgery within 1 week after randomization. Endoscopic tattooing with autologous blood and intraoperative colonoscopy will be performed by two experienced endoscopists who has more than thousands of cases colonoscopies and more than 200 cases of endoscopic mucosal resection or endoscopic submucosal dissection.

For patients who will enroll in autologous blood group, the tattooing will be performed at 24–48 hours before the surgery. When the lesion is identified by endoscopy, the patient’s peripheral venous blood will be collected using a 10 ml simple syringe without heparin preparation. Immediately after blood sampling, 2–3 ml of autologous blood will be injected submucosally at the distal side and proximal side of the lesion (about 2 cm below and above the border of the lesion) using a conventional endoscopic needle without submucosal injection of normal saline. The tattooing with autologous blood will consider to be invisible if both distal and proximal spots was not identified. For those receiving autologous blood localization, the case will be applied intraoperative colonoscopy if the autologous blood tattoo will not be identified or inaccurate in the laparoscopic colectomy.

For patients who will enroll in intraoperative colonoscopy group, the patient will be placed in the modified lithotomy position under general anesthesia with endotracheal intubation. The legs will be opened and positioned in padded stirrups to facilitate the insertion and manipulation of the colonoscope during the operation. After routine laparoscopic exploration, CO_2_-insufflated intraoperative colonoscopy will be performed using a flexible videocolonoscope. Upstream small bowel clamping will be applied before intraoperative colonoscopy. During intraoperative colonoscopy, CO_2_ pneumoperitoneum will be maintained by the insufflator so that the laparoscope could guide the colonoscope effectively.

After lesion will be identified, a standard laparoscopic colectomy will be performed by two experienced surgeons who has more than 20 years of experience in colorectal surgery with more than 200 cases per year for all enrolled patients. All abdominal operation of laparoscopy will be videotaped. Anastomosis will be performed using the instrumental method. The specimen will be pulled out through a small median incision under the xiphoid (about 3–8 cm).

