Intraoperative colonoscopy is another precise method; however, it is a somewhat complex procedure that requires an experienced endoscopist and specific instruments in the operating room. Pneumoperitoneum during laparoscopy can reduce visibility of colonoscopy and bowel distension during localization may impair the operative field for the surgeon [26].

Autologous blood was first reported by Korean researchers in 2014 [11]. The effective rates were reported from 90.9 to 92.2% based on several retrospective studies [7, 11, 27]. Autologous blood has advantages of high safety, less inflammation in that it is not a foreign material. No serious tattooing-related complication (such as perforation, colonic abscess formation, or post-tattooing fever) was reported in retrospective studies by now [7, 11, 27]. Complication related to autologous blood was also not found in in our center (data was not shown). Furthermore, this technique is simple, practical, and economic and it does not require a specialized tattooing agent or equipment to detect the target lesion. Mechanical bowel preparation before elective colorectal surgery has been used in our center. To relieve patient discomfort, doing bowel preparation once for both endoscopic tattooing and surgery. Patients receiving autologous blood tattooing underwent surgery within 24–48 h in our center. Some study reported that the longest interval between endoscopic blood tattooing and surgery was 5 days [7]. Another reason that we won’t try longer interval is that many of the previously studied localization agents (including methylene blue, ICG, and others) are absorbed and disappear within 48 h. Autologous blood maybe a good candidate agent for its persistence. We think tattooing with autologous blood can be used worldwide irrespective of the availability of tattooing agents or specialized detection equipment.

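### The six-factor logistic model for invisible tattoo would rest on about 5 to 10 events in 110 patients, so its odds ratios risk being undefined, exaggerated or too imprecise to use

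*Protocol article*

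**What the plan says.** The section 'Sample size and statistical analysis' of the protocol article plans a multivariable analysis of the effect of potential confounders "on invisible tattoo will be performed by using a logistic regression model". The factors are listed: "sex, age, body mass index, endoscopist, tumor location [colon vs. rectum], clinical tumor stage [≥ T2 vs. T1 or scars". The same section sets two-sided testing at 0.05 and names SPSS 22 as the software. It mentions no penalised or exact estimator and does not call the model exploratory.

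These statements fix how much information the model will have:

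- Arm size: "sample sizes of 110 patients in each group will be required".
- Planned rates: "success rates of 99 and 95% were assumed for the intraoperative colonoscopy group and the autologous blood group, respectively".
- Earlier evidence on blood tattooing, in the Discussion: "The effective rates were reported from 90.9 to 92.2% based on several retrospective studies".
- Definition of the outcome, under 'Intervention': "The tattooing with autologous blood will consider to be invisible if both distal and proximal spots was not identified".
- Levels of the endoscopist factor, under 'Intervention': tattooing and intraoperative colonoscopy "will be performed by two experienced endoscopists".

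**The concern.** A tattoo can be invisible only in a patient who was tattooed, so the intraoperative colonoscopy arm contributes nothing to this model. In the blood arm the event is expected to be rare, because the trial is planned on a high success rate. Six covariates are named for an outcome that may occur about five times.

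With that few events, maximum likelihood can fail outright. If all events fall in one category of a factor, its estimate runs to infinity. When the fit does converge, the odds ratios can be far from the truth and their intervals very wide.

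At stake is the only analysis in the article that asks which patients, sites or endoscopists are prone to tattoo failure. A large odds ratio could be taken as a finding, or a non-significant one as evidence that a factor does not matter, when the data support neither.

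**Working it through.** **1. The denominator.** The stated figure is 110 per group. The usual unpooled formula is n = (z₁₋α + z₀.₈)² × [p₁(1−p₁) + p₂(1−p₂)] / (margin − difference)². The variance term is 0.99×0.01 + 0.95×0.05 = 0.0574, and the denominator is (0.10 − 0.04)² = 0.0036.

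- One-sided 5%: 98.6, so 99 per arm.
- One-sided 2.5% (two-sided 5%): 125.1, so 126 per arm.

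Neither is 110. The figure does follow from 99/(1 − 0.10) = 110, but the article states no 10% dropout. The present point does not depend on this. It takes 110 as planned and shows 99 evaluable patients as a sensitivity check.

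**2. Expected events.** Events = 110 × (1 − success rate). The model has six slopes, because two endoscopists need one parameter, plus an intercept.

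| Success rate | Source | Expected events | Central 95% binomial range | Events per covariate (÷ 6) | Events if 99 evaluable |
|---|---|---|---|---|---|
| 95% | planning assumption | 5.5 | 2–10 | 0.92 | 5.0 |
| 92.2% | cited studies, upper | 8.6 | 4–14 | 1.43 | 7.7 |
| 90.9% | cited studies, lower | 10.0 | 5–16 | 1.67 | 9.0 |

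At 95% success the probability of five or fewer events is 53%. The expected 5.5 events are then fewer than the seven parameters to be estimated. Adding the control arm's expected failures (110 × 0.01 = 1.1) would raise the totals only to 6.6 and 11.1, and those are not tattoo failures.

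**3. What maximum likelihood does with this.** Simulation settings: n = 110, all six covariates entered, no true effects. The article gives no covariate prevalences, so these are assumed: sex 55%, endoscopist 50%, rectum 30%, higher stage 60%, with age and BMI standard normal. There were 2,000 trials per setting.

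| Event rate | Separated or non-convergent | Of the rest: at least one null binary factor with OR > 5 or < 0.2 | Typical upper/lower ratio of 95% CI |
|---|---|---|---|
| 5% | 38% | 29% | about 43 |
| 7.8% | 14% | 22% | about 24 |
| 9.1% | 8% | 19% | about 19 |

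The last column is exp(2 × 1.96 × SE). At 5% events the median standard error of a binary log odds ratio is 0.96, and exp(3.76) ≈ 43.

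**4. Sensitivity to the assumed prevalences.** With the four binary factors at 40, 50, 30 and 50%, separation occurred in 37%, 14% and 8% of trials at the three event rates. With rarer categories (40, 50, 20 and 30%) it rose to 52%, 26% and 20%.

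**5. False-positive rate.** Among converged fits, Wald tests at 0.05 rejected a given null binary factor in 1.7%, 2.5% and 3.2% of cases at the three event rates, all below the nominal 5%. For age and BMI the rate was about 4 to 6%. An odds ratio for a null binary factor that was both extreme and significant appeared in about 6 to 8% of converged fits.

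**6. Alternative estimator.** Firth-penalised regression gave finite estimates in over 99% of simulated trials.

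**The case against.** Four points can be made for the plan as it stands.

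- **The harm is easily overstated.** A reader might infer that the model will generate spurious significant predictors, such as one endoscopist or a rectal site. The false-positive rates above do not support that. The tests of these binary factors are conservative, and most extreme odds ratios come with intervals wide enough to show that they are uninformative. This objection stands.
- **Failure is not certain.** A reader might also infer that the estimates will be infinite. On the assumptions used, 62% of trials (at 5% events) to 92% (at 9.1%) have no separation or non-convergence. This stands too: infinite estimates are a risk, and its size depends on prevalences that the article does not give. Poor precision is present throughout.
- **The text does not name the estimator.** It does not say maximum likelihood, nor that all six factors enter together, and an analysis plan may settle both. This stands in part. The article does fix the outcome, the model type, the six factors and the software, and the usual SPSS logistic procedure uses maximum likelihood. The criticism is of that stated combination against the stated rates, not of missing detail.
- **Little depends on the model.** It is not among the objectives, the primary outcome or the secondary endpoint, and it does not enter the non-inferiority comparison. This is correct and limits the weight of the point.

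One might add that 95% is a success rate, not a visibility rate. However, the section says its rates draw on reports of successful visualisation. If invisible means that neither spot is seen, it is no broader than localization failure, so the event count could be lower still.

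**Conclusion.** The point holds as a weakness in a supporting analysis. On the protocol's own rates the model has 5.5 to 10 expected events for six covariates. That count needs only the stated arm size and success rates, with success taken as a proxy for visibility.

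The consequences rest on further assumptions: maximum likelihood, all six factors entered, no true effects and the assumed prevalences. Under these, about 8 to 38% of trials give an undefined or non-convergent fit. In the others, about one in five to three in ten show a grossly exaggerated odds ratio for a null binary factor, and intervals typically span a 20- to 40-fold range. Rarer categories make separation more frequent.

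The expected result is an unusable or over-read risk-factor table. The documents support neither certain failure nor an excess of falsely significant predictors, and the trial's primary conclusion is not affected. The change should be made because it is cheap, but the trial does not depend on it.

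**What to change.** In 'Sample size and statistical analysis':

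1. State that the model for invisible tattoo is restricted to the autologous blood arm and is exploratory.
2. Replace ordinary maximum likelihood with Firth-penalised logistic regression and profile-likelihood confidence intervals.
3. Have the investigators fix a small number of covariates before any outcome data are seen. Which of the six to keep is their choice; the documents give no basis for preferring particular ones.
4. Report the remaining factors as cross-tabulations against tattoo visibility, with exact confidence intervals.

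This is a change of wording and needs no extra patients or data. The cost is fewer adjusted estimates and the use of something beyond base SPSS. SAS is already used for the randomization list. The penalty keeps estimates finite but adds no information, so intervals will remain wide with this many events.
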